#### Screening of health education films in antenatal clinics and postnatal wards

Intervention health facilities will be provided with a TV screen and health education films about the contraceptive implant. They will be asked to screen the films daily. The films will also be shown in the waiting room of the antenatal clinic and of the postnatal clinic, so the couples will see them if and when they attend antenatal and postnatal clinics. The films have undergone an intensive development in Uganda using the person-based approach to intervention development [31] and have been approved by the Ministry of Health.

#### Supportive supervision visits

Supportive supervision visits will be undertaken at least every 2 months to VHTs and health facilities in the intervention arm, to ensure that the intervention is being delivered properly.

### Assignment of intervention or control

Clusters are at the level of the health centre III (sub-county). In all the villages surrounding a health facility, all the couples will be in the same group. Two urban and two rural health centre IIIs will be randomly selected from a list of all health centre IIIs in Mbarara District (rural) and Mbarara city (urban), in south-western Uganda. We will use a stratified randomisation according to urban/rural location. Participating health facilities will be randomised during a meeting in which the district health officer is invited to draw pieces of paper out of a hat, to determine whether each health centre is assigned to the intervention or control arm—so that the randomisation process is open and understood by all. It will not be possible to blind participants or care providers. If two of the selected sub-counties share a boundary, we will only include women intending to attend ANC and PNC in their area, in order to minimise contamination.

### Data collection and follow-up

All trial procedures are shown in the SPIRIT figure (Table 4). The questionnaires will be completed using the COSMOS digital data entry platform on smartphones (https://cosmos.tetratech.com/). This allows data entry even in the absence of a mobile phone network and upload of data at a later time into the COSMOS database. All participating VHTs will be provided with a smartphone which will remain the property of the research team until the end of the study, when the VHTs will be allowed to keep them. VHTs will pilot the use of smartphones for data entry using a training version of the COSMOS app for 2–3 weeks before starting recruitment. VHTs will be given paper case record forms to use as a backup if there are technical problems which prevent data entry on the phones. The research assistant would then enter data from paper case report forms into the electronic database. VHTs will be trained to store paper forms securely until they can be passed on to the research team.

**Table 4 Tab4:** ACCU SPIRIT figure showing the schedule of enrolment, interventions and assessments

Time point	Study period					
	Screening	Post-allocation				Close-out
	***Screening visit***	***Antenatal 1 (baseline)***	***Antenatal 2 (after 1 month)***	***Postnatal 1 (1 week after delivery)***	***Postnatal 2 (6 months after delivery)***	***Postnatal 3 (12 months after delivery)***
**Enrolment**						
**Eligibility screen**	X					
**Informed consent**	X					
**Interventions**						
***Counselling on birth planning***		X	X			
***Counselling on PPFP***		X	X	X	X	
**Assessments**						
***Relevant demographics, medical/obstetric history***		X				
***Plans for birth and PPFP***		X	X			
***Use of antenatal clinic, delivery outcomes***				X		
***Use of PPFP***				X	X	X
***Maternal and child survival outcomes***				X	X	X

### Baseline antenatal visit

After a woman has consented to take part, the VHT may continue immediately with the baseline visit or may arrange to return at a later time. However, the baseline visit should be conducted no later than 7 months of pregnancy, to allow time for the couple to engage in counselling and decision-making before the delivery. The VHT will take the woman (and her partner, if he is present) through the baseline questionnaire (Additional file 3) about her demographic characteristics, any previous pregnancies, the current pregnancy and her future intentions regarding the place of birth and postpartum family planning.

### Follow-up visits

Village health teams in all areas will attempt to follow up on pregnant women and their partners a total of four times. VHTs will perform one antenatal follow-up visit at least 1 month after the baseline (data collection about use of antenatal clinic and intentions to use birth planning and PPFP). The postnatal visits will take place at about 1 week, 6 months and 1 year after giving birth (to collect data on place of delivery, uptake of postpartum contraception, perinatal and neonatal mortality). On each occasion, they will enter data into the relevant electronic questionnaire on their smartphone. VHTs in the intervention group will deliver additional counselling and will encourage couples to attend the health facility for couples’ counselling if needed, for couples who have not yet taken up postpartum contraception.

In each health facility, health workers will be asked to report aggregate data every month on the number of women attending ANC alone or with their partners, the number of couples counselled about PPFP, the number of deliveries and the number of women provided with PPFP. All participating health centres receive a payment of 100,000 Ugandan shillings per month (about 20 UK pounds) for their help with data collection.

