**Methods:**

This is a two-group, non-blinded cluster-randomised controlled feasibility trial of a complex intervention. Primary health centres in Uganda will be randomised to receive the intervention or usual care provided by the Ministry of Health. The intervention consists of training village health teams to provide basic counselling to couples at home, encouraging men to accompany their wives to an antenatal clinic, and secondly of training health workers to provide information and counselling to couples at antenatal clinics, to facilitate shared decision-making on the most appropriate place of delivery, and postpartum contraception. We aim to recruit 2 health centres in each arm, each with 10 village health teams, each of whom will aim to recruit 35 pregnant women (a total of 700 women per arm). The village health teams will follow up and collect data on pregnant women in the community up to 12 months after delivery and will directly enter the data using the COSMOS software on a smartphone.

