### Monitoring data quality

Data entry directly into the COSMOS system minimises the risk of data loss. We will control the quality of quantitative data collection using internal controls on the COSMOS system—for example, by checking the global positioning system (GPS) location of the interview and the time taken for the interview. We will also conduct spot checks—a researcher will repeat data collection for a random sample of about 5% of participants from each village health team member to ensure that the data has been captured accurately—if significant discrepancies are found, a larger sample will be repeated for that VHT. In the electronic database, we will use standardised data capture with drop-down boxes and data entry validation. Regular debriefing sessions will be held with VHTs for review of experience and discussion of difficulties.

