### Sample size

There are four clusters—two intervention and two control areas—in the feasibility trial. In each of these areas, we will engage 10 VHTs to recruit participants. Each VHT will aim to recruit 35 women over a 6-month period, so in total, we will aim to recruit about 1400 women. A formal sample size calculation is not required for a feasibility study, but a sample of this size will allow us to estimate the key parameters for a future full-scale trial, including the variability, clustering and retention rate.

For the process evaluation, we will use a “purposive” sampling approach to select respondents (according to socio-demographic and organisational factors expected to influence the delivery or effectiveness of the intervention). We plan six separate FGDs, each of six to ten participants, two each for the following categories of individuals: (a) postpartum women—the age will determine their allocation to subgroups: adolescent girls (≤ 20 years), women 21 years and above; (b) men who are partners or husbands of women who deliver during the study; and (c) VHTs involved in the study. We will conduct about 20–30 in-depth interviews with clinic managers, health service providers, VHTs and couples. We will interview postpartum women and their partners, who took up, and who did not take up, the offer of couples’ counselling at home and at ANC and the offer of a contraceptive method, in order to understand the factors influencing their decisions, their experience of the intervention and their suggestions for improving it. We will also ask about the degree of contamination between study areas and will assess this as a feasibility outcome.

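### In the intervention arm the village health team member who counsels the woman also records her contraceptive uptake and place of delivery, and the planned 5% re-interview is not set up to compare reporting between arms.

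*Protocol article*

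**What the plan says.** **Who counsels.** The Protocol article (Intervention, Training VHTs; Table 4) has intervention VHTs counselling on PPFP at both antenatal visits and at the first two postnatal visits. Follow-up visits adds: "VHTs in the intervention group will deliver additional counselling". Control VHTs are not trained to counsel and cannot show the films, though they may give their usual health promotion advice.

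**Who collects the data.** VHTs in all areas make the antenatal follow-up visit and the three postnatal visits. The postnatal visits record where the woman delivered and whether she took up contraception. Of the VHTs the article says: "On each occasion, they will enter data into the relevant electronic questionnaire on their smartphone".

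**What the data are for.** Secondary outcomes, including PPFP uptake, are described as effect-size estimates for the main trial. Receipt of VHT counselling, and the share of VHT visits at which counselling was delivered, are primary feasibility outcomes. No sentence names their data source.

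**Partner presence and privacy.** At baseline: "The VHT will take the woman (and her partner, if he is present) through the baseline questionnaire". At follow-up, Adverse event reporting has the VHT always ask to speak separately with each partner, but links this to screening for domestic violence.

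**Checks.** Monitoring data quality lists GPS and interview-time checks, and a researcher repeat of data collection in a random sample of about 5% of each VHT's participants, with the rule "if significant discrepancies are found, a larger sample will be repeated for that VHT". No comparison between arms is described.

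**The concern.** The person asking the outcome question has a stake in the answer in one arm only. A woman may tell the VHT who counselled her on contraception that she took it up when she did not. A VHT may also record counselling more generously than it happened. The Recruitment section relies on sources and methods of data collection being similar in the two arms, but the collector's role is not similar. The article acknowledges that participants and care providers cannot be blinded. It does not discuss outcome assessment by the counsellor.

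This is a feasibility trial with descriptive analysis, so no confirmatory test is at risk. At stake are the PPFP effect sizes carried into the planning of the main trial, and the fidelity figures that show whether the intervention was delivered.

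**Working it through.** **Inputs from the Sample size section.** The design has 4 clusters, 2 per arm, with 10 VHTs in each cluster. The target is stated as follows: "Each VHT will aim to recruit 35 women over a 6-month period, so in total, we will aim to recruit about 1400 women".

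**The plan's own figure.** 4 × 10 × 35 = 1400, and 2 × 10 × 35 = 700 per arm. This agrees with the abstract: "a total of 700 women per arm".

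**Yield of the 5% re-interview.**
- Per VHT: 0.05 × 35 = 1.75, so about 2 women.
- Per arm: 0.05 × 700 = 35.
- In total: 0.05 × 1400 = 70.

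**Size of a spurious effect.** The article gives no misreporting rates, so these are assumptions. Let p be true uptake, equal in both arms, and f the share of intervention non-users recorded as users, with no such error in control. The spurious difference is (1 − p) × f.

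| True uptake p | f = 5% | f = 10% | f = 20% |
|---|---|---|---|
| 30% | 0.70 × 0.05 = 3.5 points | 7.0 points | 14.0 points |
| 40% | 0.60 × 0.05 = 3.0 points | 6.0 points | 12.0 points |

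**What the re-interview could show for one VHT.** If 20% of a VHT's records are wrong, two checks find at least one error with probability 1 − 0.8² = 0.36. At 10% wrong it is 0.19, and at 30% wrong it is 0.51.

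**What it could show by arm, with n = 35.** Exact (Clopper-Pearson) 95% confidence intervals for the share of discordant records:

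| Discordant records | Share | 95% CI |
|---|---|---|
| 0/35 | 0% | 0% to 10% |
| 2/35 | 5.7% | 0.7% to 19.2% |
| 4/35 | 11.4% | 3.2% to 26.7% |
| 7/35 | 20% | 8.4% to 36.9% |

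A 3.5 to 7 point error would appear as 0.035 × 35 = 1.2 to 0.07 × 35 = 2.5 discordant women in the intervention arm, and only if they answer the researcher differently.

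**Power to see different discordance by arm** (two-sided 5% level, 35 per arm, clustering by VHT ignored, rates assumed):

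| Control vs intervention discordance | Power with 35 per arm | Needed per arm for 80% power |
|---|---|---|
| 5% vs 10% | 12% | 435 |
| 5% vs 15% | 28% | 141 |
| 5% vs 20% | 47% | 76 |
| 5% vs 30% | 80% | 36 |

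For 5% vs 15%, 141 of 700 is about 20% of the women in each arm.

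**The case against.** Several stronger readings are tempting, and the article does not support them.

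- **The 5% repeat as the only independent check.** It is not. There are also GPS and timing checks, supportive supervision in the intervention arm at least every 2 months, monthly facility counts in both arms, and process-evaluation interviews with couples who did and did not take up counselling or contraception. What stands is narrower. The repeat is the only independent re-collection of an individual woman's data, the facility counts are aggregates, and GPS or timing cannot reveal over-reporting.
- **Contraceptive use asked in front of the partner.** Partner presence is explicit only at baseline, whereas PPFP use is collected only postnatally. At follow-up the VHT seeks time alone with each partner, although the text ties this to violence screening. Concealment from a partner would also push reported uptake the other way.
- **The enlarged sample as a bias in the data-quality result.** Nothing says that enlarged samples will be pooled with the initial ones, or that spot checks supply the outcome on correct data entry. The trigger and the larger sample size are not given, so no size can be attached. Only a conditional precaution remains.
- **VHTs rating their own counselling.** This is probable, since the VHTs complete the visit questionnaires, but the source could be the woman's own answer.

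Other objections carry weight. The questionnaires are not shown, so the order of questions may already be suitable. The repeat may already include PPFP use and place of delivery. VHT data collection is itself something the trial sets out to test. Recruitment and follow-up were under way when the article was written. None of this removes the arm difference in the collector's role or supplies a comparison of reporting between arms.

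**Conclusion.** The point holds in limited form. Counselling and outcome collection are combined in one person in the intervention arm only, and no planned comparison would show whether reporting differs by arm. The 3.5 to 7 points is an illustration resting on 30% true use in both arms, false reports from 5-10% of intervention non-users, and none in control. It is not an estimate, and the true net bias is unknown. The harm is to the effect-size estimates for the main trial and, less certainly, to the counselling-fidelity outcomes. The re-interview can expose wrongly entered or fabricated records, but about 35 women per arm will reveal only large differential error.

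**What to change.** 1. At follow-up visits, ask about PPFP use or intention and counselling received in the private moment already sought. Ask before any counselling or film at that visit, and flag visits where privacy was not possible.
2. Make sure the existing re-interview covers PPFP use, place of delivery and counselling received.
3. Report re-interview agreement by arm, with confidence intervals, beside the VHT-recorded figures. Read the effect-size estimates in that light, and state as a limitation that the counsellor collected the outcomes.
4. If re-interview results are used to estimate data accuracy, use the initial random sample only.

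**Cost.** The by-arm table needs no new data if the re-interview already covers these items. Reordering questions once follow-up has started needs ethics approval and a re-briefing of up to 40 VHTs, and it leaves data collected under two orders. It also reduces the problem without removing it, because the woman has met the VHT as a counsellor at earlier visits. A woman may repeat the same answer to the researcher, so good agreement would not prove that bias is absent. If reordering is no longer practical, items 3 and 4 can still be done.

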### Adverse event reporting

In Uganda, domestic violence is common. According to the 2016 Uganda Demographic Health Survey [37], 56% of ever-married women and 44% of ever-married men have experienced physical, sexual or emotional violence by their current or most recent spouse/partner, and one in five have experienced physical violence in the preceding year. Therefore, it is likely that some of our participants will experience this during the course of the study, although we hope that our intervention may actually reduce the risk by fostering good communication and mutual understanding between partners in a couple. Nevertheless, at follow-up visits, the VHT will always ask briefly to speak separately with each member of the couple and will then ask screening questions about domestic violence, only if it is possible to speak in private.

If VHTs become aware of domestic abuse occurring within one of the included couples, they will counsel and facilitate the victim to report the case within existing structures—initially, this would be the focal person for gender-based violence at the health facility, or the Local Council I leader who is responsible for addressing these issues and offering support as appropriate, and/or the community development officer or police. If the victim does not feel ready, the VHT will follow up and counsel her/him, with the goal of supporting her/him to disclose through the appropriate channels. The research team will monitor and report the progress of that referral as part of adverse event reporting, including a report of whether on review it is associated with being in the study or not. Any serious adverse event (resulting in hospitalisation or death) will be reported to the Mbarara University Research Ethics Committee (MUREC) using their standard serious adverse event reporting form.

### Monitoring data quality

Data entry directly into the COSMOS system minimises the risk of data loss. We will control the quality of quantitative data collection using internal controls on the COSMOS system—for example, by checking the global positioning system (GPS) location of the interview and the time taken for the interview. We will also conduct spot checks—a researcher will repeat data collection for a random sample of about 5% of participants from each village health team member to ensure that the data has been captured accurately—if significant discrepancies are found, a larger sample will be repeated for that VHT. In the electronic database, we will use standardised data capture with drop-down boxes and data entry validation. Regular debriefing sessions will be held with VHTs for review of experience and discussion of difficulties.

### Process evaluation

In complex intervention trials, it cannot be assumed that the delivery of an intervention in “real life” will be exactly as planned in the design stage of a trial. Process evaluation can lead to a greater understanding of what works or does not and provide meaningful interpretation of the effects of an intervention to inform future implementation [33, 38]. During the intervention, we will conduct a qualitative process evaluation aiming to identify operational reasons for failure or success in the implementation of the intervention and of the trial as a whole. We will assess the intervention fidelity and experiences of the intervention (in the intervention group) through ongoing monitoring and supportive supervision visits.

Qualitative data will be collected using an interview guide to capture changes in implementation or contextual factors. The interview schedules will be altered in response to emerging themes developing from analysis which will take place concurrently with data collection. This will ensure that emerging themes from earlier data can be investigated in later data collections. We will hold the interviews and focus groups at least 3 months and up to 12 months after the delivery. We will start interviews and focus group discussions at least 6 months after the start of the trial and intervention. Interviews will be conducted by a member of the research team with training and experience in qualitative research, who is fluent in the local language, Runyankole. The interviews will take place in a location such as the participant’s home or private room at a health centre, guaranteeing privacy. They will be audio-recorded and will be transcribed verbatim and translated into English where English was not the language used during the interview, omitting any names so that transcripts are anonymous. Field notes will be taken to record non-verbal communication.

### Outcomes

#### Primary process/feasibility outcomes

The following will be the primary feasibility outcomes:Percentage of eligible women who consent to participate and are recruitedPercentage of included women who:Can be followed up and provide outcome data on place of delivery and uptake of family planning: to 1 week postpartum, to 6 months postpartum and to 1 year postpartum.Whose partners agreed to participate in the projectReceived individual counselling from the VHT: on one or more occasions and at each study visitReceived couples counselling from the VHT on one or more occasionsAttended the antenatal clinic at the health centre one or more timesAttended the antenatal clinic at the health centre with their partner one or more timesReceived individual counselling at the antenatal clinic on PPFPReceived individual counselling at the antenatal clinic on birth planningReceived couples’ counselling at the antenatal clinic on PPFPReceived couples’ counselling at the antenatal clinic on birth planningWere given correct advice on the recommended place of delivery (according to their level of risk)Watched the health education films: with the VHT and at the antenatal clinicPercentage of included couples who:Were offered and attended antenatal clinics and counselling at weekendsWere counselled and consented for long-acting reversible methods of PPFPProportion of women/couples attending antenatal clinic who were offered counselling on both birth planning and use of long-acting reversible methods of PPFP at the same visitProportion of women/couples counselled who agreed on PPFP in a single session and proportion of women/couples counselled who agreed after attending extra sessionsPercentage of working days when the films on family planning are screened in antenatal clinics (in intervention areas)Percentage of VHT visits when:Counselling was delivered to the woman/couple about birth planning/family planningData was correctly entered directly into the COSMOS app on the smartphoneCosts of intervention/control—health economics

